**Figure 3 F3:**
[figure not shown]
Stepped wedge randomisation of study sites. HCC, hepatocellular carcinoma.

#### Inclusion/exclusion criteria

Participants identified in the liver check phase as having clinically significant liver disease will be eligible to take part in this phase (table 2). Nil exclusion criteria.

**Table 2 T2:** Inclusion and exclusion criteria for the liver monitoring phase (HCC surveillance)

Inclusion criteria	Exclusion criteria
Participants with compensated advanced chronic liver disease (cACLD) or cirrhosis identified during the screening phase by any of the following: Clinically diagnosed on the basis of clinical and radiological features, or Liver stiffness score>12 kPa, or Hepascore≥0.8 or liver outcome score for HCC of ≥10% at 5 years (if FibroScan® unavailable) Liver stiffness score>10 kPa if participants have higher clinical risk factors (age>50 years, multiple liver risk factors or thrombocytopaenia). Participants with chronic hepatitis B virus infection, without cirrhosis, who are >50 years	Nil

HCC, hepatocellular carcinoma.

#### Randomisation

The four participating sites (groups) will be the unit of randomisation in the 24-month stepped-wedge RCT design. The sequence in which these four sites cross over from the 'usual care’ control period to the 'On-Country’ intervention period will be randomly determined. An independent statistician with no involvement in participant recruitment will generate the random allocation sequence using a computer-based random number generator with statistical software (Stata, StataCorp, US). Each site will begin the trial receiving usual care surveillance for a minimum of 6 months, and the randomisation sequence will determine at which 6-month time point each site transitions from usual care to the On-Country surveillance. The generated allocation schedule will list the 24-month care sequence for each site (A, B, C and D) and will be securely stored and concealed from the core study team until the point of implementation to prevent any potential bias. The four sites will be assigned a site code (A, B, C or D) by the investigators prior to receiving the allocation schedule from the biostatistician. Given the small number of sites, stratification will not be used.

#### Usual HCC monitoring (control)

Usual HCC surveillance (control group) will involve participants receiving 6-monthly liver ultrasound and serum AFP tests as per their site’s usual care processes. This will involve participant travel to the closest regional imaging service for liver ultrasound, with each scan reviewed and reported by a qualified radiologist.

#### On-Country HCC monitoring (study intervention)

On-Country surveillance will involve participants receiving 6-monthly liver ultrasounds and serum tumour (AFP and GAAD) tests On-Country. The On-Country liver ultrasounds will be performed by a specialist ultrasonographer using a mobile ultrasound (Sonosite PX Ultrasound System) for detection and assessment of liver lesions, with each scan reviewed and reported by a qualified radiologist. The blood draw for the serum tumour tests will be conducted at the local ACCHS. The duration of the monitoring period will vary as per the stepped-wedge design and allocation schedule.

Surveillance ultrasound will be considered positive if it detects a liver lesion ≥10 mm in maximal diameter and combined with elevated serum AFP as per current guidelines. If an HCC diagnosis is suspected, participants will be referred to the existing care pathways for diagnosis, treatment and management.

##### Sample size and power calculations

The study is powered to detect a clinically meaningful difference in adherence to HCC surveillance. With four sites and a minimum of 10 participants per site (total n=40), the study will have 80% power to detect an absolute difference of 24 percentage points in adherence between the control and On-Country surveillance periods (eg, an increase from 10% in the control periods to 34% in the intervention periods). This calculation is based on a two-sided alpha of 0.05 and assumes four measurement periods over 24 months (one during the initial baseline control period for all sites, followed by three 6-monthly measures). It further assumes an intra-class correlation coefficient of 0.05 to account for the correlation between participants within the same site. To ensure a final analytic sample of at least 40 participants, we will recruit 45 individuals to allow for a potential attrition rate of approximately 10%.^42^ The overall 24% difference in adherence between care types is a conservative estimate of anticipated improvement, based on our published experience of 64% improvement in 2-year surveillance following a clinical practice improvement programme in a metropolitan hospital setting (44). The estimated 10% adherence in the control period is also conservative given much lower values described in current literature.^43^

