**Figure 2 F2:**
[figure not shown]
Screening and Suveillance of Liver Disease in Indigenous Australians (SSOLID) study design.

This study will take place in four very remote (Modified Monash 7) Indigenous Australian study sites (11 communities) across SA and Western Australia (WA). The sites are the Anangu Pitjantjatjara Yankunytjatjara (APY) Lands East in SA, including Mimili, Kaltjiti and Iwantja communities; the APY Lands West in SA, including Pukatja, Amata and Pipalyatjara communities; Coober Pedy in SA and the East Pilbara region in WA, including Jigalong, Parnngurr, Punmu and Kunawarritji communities. The research team will work with the local ACCHSs at each site to implement the study and ensure it meets local community needs, and this partnership will be formalised via a clinical trial agreement.

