### Phase 2: Liver Check (Screening)

The liver check phase has a screening design (12 months) and will identify people with clinically significant liver disease eligible for Phase 3. In the liver check phase of the project, the site PI, IPO and support ACCHS staff will review the primary healthcare patient databases to ascertain participants who meet study inclusion criteria for screening (table 1). Recruitment will be via invitation only and led by the site PI and IPO. Participating study sites will aim to screen approximately 100 participants at their site. The liver health check will involve a review of the participant’s medical history and a blood test for liver function and serum fibrosis assessment (FIB-4 and Hepascore) and will be completed On-Country at the local ACCHS. A positive indirect (FIB-4≥1.3) or direct (Hepascore ≥0.6) fibrosis test result will trigger a FibroScan® assessment. The FibroScan® assessment will be done On-Country by the local site team. All participants will be recompensed for their time and contribution to the study.

**Table 1 T1:** Inclusion and exclusion criteria for the liver check phase

Inclusion criteria	Exclusion criteria
Aboriginal and/or Torres Strait Islander descent Aged ≥25 years Defined by the prevalence of liver disease at lower age groups and the aim to focus the study on the population who will benefit the most. Able to provide informed consent Has at least one risk factor for liver disease: Body Mass Index (BMI) >30 Current chronic hepatitis B virus Hepatitis C virus (current or past infection) Type 2 diabetes Unknown hepatitis B vaccination status Current or past alcohol misuse (an Alcohol Use Disorders Identification Test-C score of≥3 for women and ≥4 for men or clinical notification of alcohol misuse) Abnormal liver function tests (above normal range)	Unable to provide informed consent <25 years of age No known risk factors for liver disease

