A FibroScan® result of >12 kPa, or if a participant has chronic hepatitis B and is >50 years of age, will trigger eligibility into Phase 3 of the study. Participants with a FibroScan® result of >10 kPa will have their overall risk profile for HCC reviewed by the medical monitor to determine entry into Phase 3 of the study. Participants with higher clinical risk factors (age>50 years, multiple liver risk factors or thrombocytopaenia) will be entered into the HCC monitoring phase with this lower liver stiffness measurement cut-off of >10 kPa.^41^ In the event, a FibroScan® assessment is unable to be performed on a participant with elevated fibrosis tests, a Hepascore≥0.8 or a liver outcome score for HCC risk≥10% at 5 years will be used as the cut-off to identify participants with cACLD. Based on conservative estimates of a prevalence of significant liver disease in 20% of screened participants, we anticipate that each site will be able to recruit approximately 10 participants for Phase 3 of the study assuming a consent rate of 50%.

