### Yarning data

Our research yarning will focus on understanding liver disease, experiences of different models of care and costs incurred by participants, and what participants think works well in their communities when it comes to accessing liver health checks and monitoring. Yarns will be conducted at the end of the liver check and liver monitoring phases. Additional yarns will be conducted with site-based health service staff to explore experiences and perspectives relating to (i) current liver care at the health service and any barriers to providing care and (ii) changes to the service after provision of the study education and availability of On-Country monitoring. We will use the site PIs and IPOs, and community networks, to recruit participants for these yarns. We will have recruitment information in both English and relevant Indigenous languages that can be distributed through these networks and displayed in common areas within each community. Yarns will be undertaken by Indigenous Australian investigators and will be offered in groups as well as one-on-one yarns to prioritise participants’ preferences and comfort. We aim to yarn with 6–8 participants at each community at the end of each study phase. Guidelines for all involved in the yarning circles around confidentiality and information sharing within the sessions will be set up by each CLG and will be explicit and discussed prior to the session commencing. All participants will be recompensed for their time and contribution to the yarns.

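### The screening projection yields about 40 Phase 3 recruits, but the sample size calculation needs 45 and counts the same 10 per site as the number left after attrition

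*Protocol article*

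**What the plan says.** Two sections of the protocol article give figures for the size of Phase 3.

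- **Phase 2: Liver Check (Screening)** sets the intake: "Participating study sites will aim to screen approximately 100 participants at their site". It then works forward: "Based on conservative estimates of a prevalence of significant liver disease in 20% of screened participants", followed by "we anticipate that each site will be able to recruit approximately 10 participants for Phase 3 of the study assuming a consent rate of 50" per cent.
- **Sample size and power calculations** takes four sites with a minimum of 10 participants each (n=40). It claims 80% power for a 24-point difference in adherence (for example 10% to 34%), with two-sided alpha 0.05, four measurement periods and an intra-class correlation of 0.05. It then adds: "To ensure a final analytic sample of at least 40 participants, we will recruit 45 individuals to allow for a potential attrition rate" of roughly 10%.

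The number of sites is fixed by the Randomisation section: "The four participating sites (groups) will be the unit of randomisation in the 24-month stepped-wedge RCT design". The Phase 3 inclusion criteria draw participants from those identified in the liver check phase. Under Study design and settings, that phase ends in September 2026 and Phase 3 starts in October 2026.

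**The concern.** The figure of 10 per site has two incompatible meanings. In the screening section it is the expected number recruited, before anyone is lost. In the sample size section it is the minimum left for analysis, after about 10% are lost. A sponsor following the screening plan exactly would expect to enrol 40, not 45.

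The power statement has no margin below 40. The supply is also bounded, because Phase 3 recruits come only from the liver check phase, which closes before Phase 3 opens. A shortfall found at the end of screening cannot be made up under the timetable as written.

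**Working it through.** **Inputs from the protocol article.** Sites: 4. Screened per site: about 100. Prevalence: 20%. Consent into Phase 3: 50%. Analysed sample required: 40 (10 per site). Attrition: about 10%. Recruitment target: 45.

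**1. Reproduce the plan's own target.** 40 / (1 − 0.10) = 44.4, rounded up to 45. The inflation is correct. In the other direction, 45 × 0.90 = 40.5, or about 10.1 per site.

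**2. Screening yield.** Per site: 100 × 0.20 × 0.50 = 10. Total: 4 × 10 = 40. Shortfall against the target: 45 − 40 = 5 (11% of 45).

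**3. After the plan's own attrition.** 40 × 0.90 = 36, or 9 per site, which is 4 below the stated 40.

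**4. What would close the gap, changing one input at a time.**
- Screening: 45 / (0.20 × 0.50) = 450 in total, 112.5 per site, so about 113.
- Prevalence: 45 / (400 × 0.50) = 22.5%.
- Consent: 45 / (400 × 0.20) = 56.25%.

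**5. Effect on power, taking the stated 80% at 40 as given.** For 80% power, the difference divided by its standard error is 1.960 + 0.842 = 2.802. If the standard error scales with one over the square root of the number per site, it grows by √(10/9) = 1.054.
- Power: 2.802 / 1.054 − 1.960 = 0.698, which corresponds to about 76%.
- Detectable difference at 80% power: 24 × 1.054 = 25.3 points. This is an upper figure, because any between-site part of the variance does not grow when fewer people are seen per site.

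**6. Cross-check on a stepped-wedge model.** This is a linear model with 4 sites, 4 periods, intra-class correlation 0.05 and 10% against 34%. Crossovers are assumed at 6, 12 and 18 months, with two sites sharing one of these steps (the design figure is not shown). The article does not state its variance or within-person correlation assumptions, so two sets that come close to 80% were tried.

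| Assumption | Shared step | 10 per site | 9 per site |
|---|---|---|---|
| Control-rate variance, independent repeated measures | 6 or 18 months | 83.7% | 80.2% |
| Control-rate variance, independent repeated measures | 12 months | 79.9% | 76.0% |
| Pooled variance, within-person correlation 0.5 | 6 or 18 months | 80.9% | 76.8% |
| Pooled variance, within-person correlation 0.5 | 12 months | 77.9% | 73.7% |

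The loss from 10 to 9 per site is 3.5 to 4.2 points, in line with step 5.

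**The case against.** The strongest reply is that the two figures differ in kind. The screening section gives a cautious feasibility projection, hedged as approximate and built on a prevalence called conservative. The sample size section gives a target. A projection five below a target does not show that the target will be missed, and step 4 shows how little is needed to reach it. Eligibility also includes people over 50 with chronic hepatitis B without cirrhosis, and the article does not say whether the 20% counts them. This stands as a reason to call the gap modest. It does not remove the inconsistency: 10 per site is the number the article says it anticipates for Phase 3, and no higher expectation is given.

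A second reply is that 36 counts completers. The primary analysis includes all randomised participants in a repeated-measures model, so someone who leaves late still contributes earlier periods, and the true loss of information may be smaller. This also stands. However, the sample size section itself treats attrition as loss from the analytic sample, and 36 follows from that convention.

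A reader might go further in two directions that the document does not support.

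- **That the trial will probably miss its sample.** One could treat the yield as exactly 10% of exactly 400 and compute a low chance of reaching 45. The inputs are approximate and called conservative, so such a probability would be falsely precise and is not evidence of likely failure.
- **That the yarning target is impossible.** The Yarning data section says: "We aim to yarn with 6–8 participants at each community at the end of each study phase". With 11 communities that is 66 to 88 people per round, more than the 45 Phase 3 recruits. But the round after Phase 2 can draw on about 400 screened people. For the round after Phase 3, recruitment runs through site staff and community networks and is not limited to Phase 3 participants. At most the intended group could be stated more clearly; it is not an arithmetic error.

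**Conclusion.** The inconsistency holds and needs no outside assumption: the screening inputs project about 40 recruits, the sample size section requires 45, and 10 per site is used both before and after attrition. On the plan's own figures about 36 would complete instead of 40.

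The consequence is small to moderate: about 4 points of power (80% to about 76%), or about 1 point of detectable difference (24 to about 25). That size rests on accepting the stated 80% at 40 participants and on treating attrition as full loss from the analysis. The severity is minor to moderate. The point is about figures that must agree, and it does not show that recruitment will fail.

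**What to change.** Reconcile the liver check section with the sample size section in one of two ways.

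1. **Keep the screening target.** State that about 40 will be recruited and about 36 analysed (9 per site), and restate the power and detectable difference for that number. This costs nothing beyond the text, but the stated power falls or the detectable difference rises as shown above.
2. **Keep the recruitment target of 45.** State a screening number consistent with it: about 450 in total, or 113 per site, at 20% prevalence and 50% consent. This costs about 50 more liver checks (450 − 400). If a higher prevalence or consent rate is expected instead, state that value.

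In either case, say whether 10 per site is meant before or after attrition. The second option has to be settled while liver check screening is still open.

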## Data collection

### Consent

Participant information and consent forms will be in English and in relevant Indigenous languages (example in online supplemental file 1). Informed consent will be obtained via the site PIs and IPOs and will include an audio-visual presentation of participant information. Consent will be obtained for involvement in the study, for taking samples, for recording yarns and for accessing Services Australia data for economic analysis. Data collected will be used expressly for approved activities exclusively for this research project. Specified consent will be obtained from participants, and no data collected will be used for a secondary or unspecified purpose.

### Quantitative data

Participant sociodemographic and clinical information will be collected at the Liver Check phase (prior to randomisation), namely age, sex, relevant medical history (eg, liver disease risk factors), blood test results (including liver function tests) and serum fibrosis assessments (FIB-4 and Hepascore). Outcome data (adherence to HCC surveillance) will be collected prospectively during the liver monitoring phase, including dates liver ultrasound, AFP and GAAD tests are performed.

### On-Country liver ultrasound data

The adequacy of the On-Country ultrasound exam for the exclusion of liver lesions, including HCC, will be obtained using standard scoring systems of visualisation.^44^ The following visualisation criteria will be applied: (i) no or minimal limitations, defined as any limitations that are present but unlikely to meaningfully affect the sensitivity in the detection of masses; (ii) moderate limitations, defined as the presence of any limitations that may decrease the sensitivity of detecting small masses and (iii) severe limitations, defined as any limitations that significantly lower the sensitivity of focal liver observations.^45^

### Yarning data

Our research yarning will focus on understanding liver disease, experiences of different models of care and costs incurred by participants, and what participants think works well in their communities when it comes to accessing liver health checks and monitoring. Yarns will be conducted at the end of the liver check and liver monitoring phases. Additional yarns will be conducted with site-based health service staff to explore experiences and perspectives relating to (i) current liver care at the health service and any barriers to providing care and (ii) changes to the service after provision of the study education and availability of On-Country monitoring. We will use the site PIs and IPOs, and community networks, to recruit participants for these yarns. We will have recruitment information in both English and relevant Indigenous languages that can be distributed through these networks and displayed in common areas within each community. Yarns will be undertaken by Indigenous Australian investigators and will be offered in groups as well as one-on-one yarns to prioritise participants’ preferences and comfort. We aim to yarn with 6–8 participants at each community at the end of each study phase. Guidelines for all involved in the yarning circles around confidentiality and information sharing within the sessions will be set up by each CLG and will be explicit and discussed prior to the session commencing. All participants will be recompensed for their time and contribution to the yarns.

## Data analysis

This project will incorporate a multi-methods approach to data analysis with integration between IRM and QRM analysis to ensure outcomes have a site-specific context and are within the knowledge interface (figure 4). The primary outcome is the difference in adherence to HCC surveillance between usual care surveillance and On-Country surveillance. Adherence to HCC surveillance is defined as the proportion of participants in which HCC surveillance was undertaken. Secondary outcomes include the acceptance and feasibility of the On-Country liver health model, the cost-effectiveness of the On-Country model compared with usual care, and the adequacy of liver ultrasound examination.

**Figure 4 F4:**
[figure not shown]
SSOLID methodology.

### Primary outcome

The primary analysis will be conducted on a modified intention-to-treat (ITT) basis, where all participants that are randomised are included in the analysis and are assigned to their original treatment according to the randomised crossover schedule, regardless of treatment received. Adherence to HCC surveillance will be operationally defined as a binary variable and recorded for each participant during each 6-month (±2 months) study period. A participant will be considered 'adherent’ (coded as 1) if they complete both a liver ultrasound and the required serum biomarker tests within that period; otherwise, they will be 'non-adherent’ (coded as 0). Analysis of the binary adherence outcome will be performed using a generalised linear mixed-effects model (GLMM) with a logit link function. The model will include fixed effects for the treatment (usual care vs On-Country), time (as a 6-month categorical variable) and time x treatment. To account for the clustered data structure, random intercepts for site and for participant (to account for repeated measures on individuals and for repeated measures within each site). The primary intervention effect will be reported as the estimated marginal mean difference in proportions (95% CI) for On-Country versus usual care surveillance. We will also report the odds ratio (95% CI) for adherence for On-Country versus usual care surveillance. Missing outcome data will be investigated for patterns, and, if assumed to be missing at random, we will conduct a sensitivity analysis using a GLMM with multiply imputed datasets to ensure our findings remain robust. Subgroup analyses by site, gender, age and liver aetiology will be conducted depending on the final number of participants recruited.

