### Phase 3: Liver Monitoring (HCC surveillance)

The liver monitoring phase is a 24-month stepped-wedge RCT to compare two models of HCC surveillance (usual care vs On-Country monitoring) for Indigenous Australians who live in very remote communities. The stepped-wedge RCT design is both justifiable and optimal—relative to a conventional parallel clustered trial—in very remote Indigenous Australian community settings because of the small number of sites and because it does not exclude anyone from access to treatment, which could further exacerbate inequities. All sites will have between 6 months and 18 months of usual care before commencing the On-Country HCC surveillance period at different time intervals, which will continue for 6–18 months depending on randomisation allocation (figure 3).

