#### Economics analysis

Generalised linear mixed models will be used to compare differences in costs between the surveillance and control steps of the trial, using the same fixed and random effects as specified for the outcomes analysis. The primary cost-effectiveness endpoint is the incremental cost per additional eligible individual undergoing surveillance, which will be estimated by dividing the difference in the total costs of surveillance across the surveillance and control steps of the trial by the difference in the surveillance prevalence. To represent parameter uncertainty, non-parametric bootstrapping with replacement will be undertaken to generate 5000 bootstrap replicates of the cost and outcome variables. The results of a recently published modelled economic evaluation of 6-month HCC surveillance will be used to extrapolate the effects of observed effects of the intervention on surveillance. In people with cirrhosis, this study reported that 6-monthly HCC surveillance can increase early-stage diagnoses to up to 81% and reduce HCC mortality by 22%.^47^

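### The primary model's time-by-treatment interaction is only partly identified in this stepped wedge, so the single difference and odds ratio the plan reports are not defined as written

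*Protocol article*

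**What the plan says.** The Primary outcome section specifies a logistic mixed model with random intercepts for site and participant. On the fixed part it says: "The model will include fixed effects for the treatment (usual care vs On-Country), time (as a 6-month categorical variable) and time x treatment". It then promises one summary: "The primary intervention effect will be reported as the estimated marginal mean difference in proportions (95% CI) for On-Country versus usual care surveillance". A second single summary follows: "We will also report the odds ratio (95% CI) for adherence for On-Country versus usual care surveillance". Participants are analysed as "assigned to their original treatment according to the randomised crossover schedule, regardless of treatment received", so the condition in the model follows the schedule.

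The schedule is set elsewhere in the article. Randomisation: "Each site will begin the trial receiving usual care surveillance for a minimum of 6 months". Phase 3: "All sites will have between 6 months and 18 months of usual care before commencing the On-Country HCC surveillance period", and of the On-Country period, "which will continue for 6–18 months depending on randomisation allocation". The sample size section counts four measurement periods over 24 months, the first all control, and powers one overall difference of 24 points (10% versus 34%).

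The Economics analysis section compares costs "using the same fixed and random effects as specified for the outcomes analysis".

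**The concern.** A full interaction between categorical period and treatment gives each period its own treatment effect. Estimating that effect needs both conditions within the period. In this design the first and last periods each contain one condition only, so half of the period-specific effects have no data behind them.

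The plan nevertheless asks this model for one marginal difference and one odds ratio. Depending on its defaults, software would report the quantity as not estimable or silently drop aliased columns and label whatever remains as the treatment effect. The primary result would then rest on a coding default or on a choice made after the data are seen. The cost comparison, the numerator of the cost-effectiveness ratio, would have the same fault.

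**Working it through.** **1. Which cells exist.** There are four 6-month periods. Usual care lasts at least 6 months, so period 1 is all usual care. It lasts at most 18 of 24 months, so period 4 is all On-Country. The stepped-wedge figure is not available, so I took every way in which four sites can use the three crossover points (after 1, 2 or 3 periods) with each point used: (1,1,2,3), (1,2,2,3) and (1,2,3,3).

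| Period | Sites in usual care | Sites On-Country |
|---|---|---|
| 1 | 4 | 0 |
| 2 | 2-3 | 2-1 |
| 3 | 1-2 | 3-2 |
| 4 | 0 | 4 |

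Six of the eight cells are filled. Coding by schedule means that off-schedule care cannot fill the other two.

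**2. Rank.** Columns: intercept 1 + treatment 1 + time 3 + interaction 3 = 8. Write D for On-Country and P2, P3, P4 for the period indicators, with period 1 as reference. There are two exact dependencies:
- D×P4 = P4, because everyone is On-Country in period 4.
- D = D×P2 + D×P3 + D×P4, because nobody is On-Country in period 1.

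The rank is 8 − 2 = 6. A numerical check gives 6 in all three layouts. Without the interaction there are 5 columns and the rank is 5. The link function and the random intercepts do not alter this, since the deficiency is in the fixed effects.

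**3. What can be estimated.** The period-2 effect, the period-3 effect, their difference and their average can. The period-1 and period-4 effects cannot, nor can any average that includes them.

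**4. What the treatment coefficient would mean.** With period 1 as reference and later columns dropped first, D×P3 and D×P4 go and the coefficient of D is the period-3 effect. With period 2 as reference, D×P1 is all zeros, D×P4 equals P4, and the coefficient of D is the period-2 effect. The data are the same and the primary result differs.

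**5. Reproducing the plan's power.** I used the Hussey-Hughes variance with additive period and treatment effects: I = 4 sites, T = 4 periods, m = 10, ICC 0.05, layout (1,2,2,3), and outcome variance v = 0.10 × 0.90 = 0.09.
- Site variance τ² = 0.05 × 0.09 = 0.0045. Variance of a site-period mean s² = 0.95 × 0.09 / 10 = 0.00855.
- U = 8 (On-Country site-periods), W = 1² + 3² + 4² = 26, V = 3² + 2² + 2² + 1² = 18.
- Var = I s²(s² + Tτ²) / [(IU − W)s² + (U² + ITU − TW − IV)τ²] = 4 × 0.00855 × 0.02655 / (6 × 0.00855 + 16 × 0.0045) = 0.000908 / 0.1233 = 0.00736, so SE = 0.0858.
- Power = Φ(0.24/0.0858 − 1.96) = 0.799.

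The stated 80% is therefore that of a model without the interaction.

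**6. Precision with and without the interaction.** The same method, a linear approximation to the logistic model, now uses the average of the two binomial variances, (0.09 + 0.34 × 0.66)/2 = 0.1572. Ranges are over the three layouts. The single-period values come from fitting separate treatment columns in periods 2 and 3 by generalised least squares.

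| Effect | SE, no participant correlation | Power for 24 points | Power if half the within-site variance is between participants (assumption) |
|---|---|---|---|
| One period (2 or 3) | 0.135-0.156 | 34-43% | 55-68% |
| Average of periods 2 and 3 | 0.109-0.113 | 56-60% | 81-83% |
| Common effect, no interaction | 0.108-0.113 | 56-60% | 81-84% |

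Examples: Φ(0.24/0.135 − 1.96) = 0.43 and Φ(0.24/0.156 − 1.96) = 0.34. With the variance that reproduces the plan (0.09), one period gives 53-65% and the common effect 80-84%.

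**The case against.** The strongest defence is that the interaction is not wholly unidentified. One of its three degrees of freedom, period 3 against period 2, is estimable. The article does not say that the marginal difference runs over all four periods. An average over the two mixed periods is a legitimate effect, does not assume constancy, and costs almost no precision (step 6). All of this stands. It limits the point without answering it, because the article does not restrict the average to those periods or say which odds ratio is meant.

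Two stronger readings are tempting. A reader might infer that the design cannot yield a treatment effect once the interaction is present. The documents do not support that, since periods 2 and 3 contain both conditions. A reader might also infer that the interaction cuts power from the stated 80% to 34-43%. That mixes two variance assumptions: under the average variance used for 34-43%, the model without interaction itself has only 56-60%. The loss also arises only if one period's coefficient is taken as the result.

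Nor is this a detail left to a fuller analysis plan. The article states both the model and the summary, and the two do not fit together.

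**Conclusion.** The point holds in this limited form. The stated primary model has fixed effects of rank 6 of 8. It identifies the treatment effect in periods 2 and 3 only, and does not supply the single marginal difference and odds ratio that the article promises. That follows from the stated schedule and needs no numerical assumption beyond both conditions being present in periods 2 and 3.

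The size depends on what is finally reported. If one period's coefficient is used, power is about 17 to 26 points lower than for a common effect under average binomial variance, ICC 0.05, 10 per site and no participant correlation (for example 60.5% − 42.8% = 17.7 and 60.5% − 33.7% = 26.8 in the unbalanced layouts). If the period 2-3 average is used, the loss is negligible. All the power figures use a normal test with four sites and a linear approximation. The undefined primary effect is the main fault, and it warrants correction before data are seen.

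**What to change.** Preferred: delete the time-by-treatment term from the primary model. Keep treatment, categorical period and the random intercepts, and report the one period-adjusted treatment effect as a risk difference and an odds ratio. This matches the single effect in the sample size section. Make the same deletion in the cost model. Examine a changing effect as a sensitivity analysis, for example by time since crossover. The cost is one sentence in each section and the assumption of a constant effect in the primary analysis.

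Alternative: keep the interaction, but state that the primary effect is the average over periods 2 and 3, where both conditions occur, and define the odds ratio and the cost difference over the same periods. This avoids assuming a constant effect, at almost the same precision, but the result then describes only those two periods.
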